[figure not shown]

**A. FULL TITLE OF THE PROTOCOL**

A Comprehensive Meditation and Breath Program (SKY) as an Adjunct Tool to Increase Resilience and Wellness in Frontline Healthcare Workers – A Randomized Pilot Study

**Nature of the Study:** Individual Research Project

## C. INFORMATION ABOUT RESEARCH

**Research Center:** Online

**Type / Subject / Design of Research:** Survey studies

### **Rationale / Purpose of the Research:**

The current COVID-19 pandemic has resulted in great physical and mental strain on frontline healthcare professionals who are already at high risk for these conditions, including significantly increased anxiety and depression. This is due to many factors, including lack of adequate protective equipment, fear of contracting the virus, fear of spreading it to loved ones, and the necessity to frequently make important decisions about the life and death of patients. Therefore, there is an urgent need to intervene to reduce the impact of these factors on the psychological health of health workers to protect them and the health system from harmful consequences. Various tools to regulate and support psychological health have been developed for pandemics, but their effectiveness has not yet been conclusively tested. Among the most widely used methods in this context are meditation and breathing programs, one of which is Sudarshan Kriya Yoga (SKY). SKY is a comprehensive program that uses specific breathing exercises to eliminate stress, support various organs and systems in the body, transform disturbing emotions and promote inner peace. Research on SKY, published in international scientific journals, has shown significant positive effects on various aspects of participants' physiology and psychology. The aim of this project is to systematically examine the possible impact of SKY on the psychological health of healthcare professionals working with the COVID-19 pandemic. The studies will include psychological assessment through self-report standardized questionnaires on various aspects of health and resilience. Our hypothesis is that SKY will reduce psychological distress, increase resilience, and trigger positive changes.

Our preliminary data from surveys conducted after the SKY programs offered to over 1700 frontline health professionals in Turkey and Portugal during the pandemic supports our hypothesis that SKY can make significant tangible contributions to various aspects of wellness in frontline healthcare workers. This planned pilot clinical trial will test this hypothesis and the feasibility of SKY in this context; if the results are positive, this will be the basis for larger clinical trials.

### **Materials and Methods:**

Volunteers who are medical doctors working with the COVID-19 pandemic will be divided into 2 groups: experimental group and control group. **EXPERIMENTAL GROUP:** The SKY program will be implemented. It includes gentle stretches, specific breathing exercises, and cognitive coping and stressor assessment strategies. Subjects are first trained in SKY for 3 consecutive days for 1.5 hours each. They then apply what they have learned in during the intervention as a daily home practice (about 30 minutes) throughout the research period. In addition, subjects participate in weekly group follow-up sessions of approximately one hour that includes group practice and a Q&A session regarding their home practice is.

Breathing techniques that are part of SKY are: (a) Ujjayi or "Victory Breath" with 'three-stage-pranayama practice, (b) three sets of Bhastrika or "Bellows Breath", and (c) SK, a rhythmic breath meditation program, practiced in this order. All practices are done in a sitting position on a chair or on the floor. Eyes are kept closed throughout the sessions.

**CONTROL GROUP:** Stress management training (SMT) will be conducted for 1.5 hours a day for three consecutive days. The training will consist of various video resources explaining how one can reduce stress, including cognitive coping strategies (e.g. <https://www.youtube.com/watch?v=hpmST69N3Zk>). Similar to the experimental group, there will be weekly follow-up sessions for the control group, lasting approximately one hour, where the material

---

used during the main 3-day program will be reviewed and questions answered.

A total of 200 health professionals will be randomized into two study arms of 100 each: experimental group and control group. The target for each group is 80 subjects, but to account for dropout/exclusion, 100 subjects per group will be included (with an expected dropout/exclusion rate of 20%). Both groups will be pretested at the time of recruitment into the study. The experimental group and the control group will be divided into two and the trainings will be delivered in two groups.

Two days after the training, the tests will be done again (Posttest 1) in a similar way to the pretest. Eight weeks after Posttest 1, Posttest 2 will be performed using the same parameters. The data obtained will be compared within and between the experimental and control groups at these three different times.

Below is a brief flowchart of the study timeline:

Weeks 1-3 Inclusion of participants

Week 4 PreTest

Week 4/5 SKY

Week 4/5 Posttest 1

Week 12/13.

Week Posttest 2

Psychological well-being parameters will be assessed using standardized questionnaires at the time points described above. The questionnaires to be used are described in the "Procedures and Variables to be used in the Study" section.

---

|                                        |     |
|----------------------------------------|-----|
| Estimated Number of Volunteers: | 200 |
|----------------------------------------|-----|

---

|                                         |                                                                                                                                                                   |
|-----------------------------------------|-------------------------------------------------------------------------------------------------------------------------------------------------------------------|
| Volunteer Group Characteristics: | - >Over 18 years of age
- Female and Male
- Healthy
- Active physicians and nurses
- (100 subjects in each of the control and the experimental group) |
|-----------------------------------------|-------------------------------------------------------------------------------------------------------------------------------------------------------------------|

---

#### **Inclusion and Exclusion Criteria:**

**Inclusion criteria:** 25-65 of age; ability to speak/read Turkish and give informed consent; interest in being part of a study to evaluate breath-derived exercises, willingness to do some form of relaxation exercise every day for 2 months, active practicing physician.

**Exclusion criteria:** Psychiatric illness or other major illness such as bipolar disorder, chronic PTSD, schizophrenia or schizoaffective disorder, uncontrolled hypertension, lung disease, liver disease, cancer, or heart disease. Currently practicing a mind-body program regularly, such as meditation, yoga and breathing techniques. Note: These criteria will be specified in a form that the subjects will fill in when they apply to be included in the study.

Information obtained during the application will be stored in a keyword-protected file on a keyword-protected computer until the end of the study and then deleted.

---

**Control Group :** Inclusion and exclusion criteria for the control group is identical with the experimental group.

---

#### **Procedures and Variables to be used in the Research:**

The parameters of psychological well-being in the subjects will be assessed by administering the standardized questionnaires listed below:

1. Depression, Anxiety and Stress Scale (DASS)-42: A set of three self-report scales designed to measure the negative emotional states of depression, anxiety and stress (Lovibond and Lovibond, 1995).

2. Professional Satisfaction Index (PFI): A brief instrument to assess both burnout and professional satisfaction in physicians (Trockel et al., 2018).

3. Life Orientation Test - Updated (LOT-R): A 10-item self-report scale measuring expectations about positive outcomes in general (Scheier et al., 1994).

---

4. Regensburg Insomnia Scale (RIS): A self-report scale to assess cognitive, emotional, and behavioral aspects of psychophysiological insomnia (Crönlein et al., 2013)

---

**Estimated Research start date:** 15/06/2021

**Estimated duration of the research:** 6 Months

---

## D. COMMITMENT STATEMENT

- The information in the application file is correct.
- The research will be conducted in accordance with the protocol, relevant legislation, Izmir Biomedicine and Genome Center Non-Interventional Ethics Committee Directive, current Helsinki Declaration and Good Clinical Practice principles,
- In case of changes in the research team or changes in the purpose, method, etc. in the research protocol, we will notify your board before the said change is made.
- We confirm that no non-routine procedures such as tests, laboratory examinations, physician examinations, use of chemicals and medical devices, etc. to be performed within the scope of this research; any such procedures will not be covered by public funds and budgets or private health insurances or by the subjects themselves, and that such costs will be paid by the person or organization supporting the project.
- I have read the Good Clinical Practices (GCP) Guideline put into effect by the Republic of Turkey Ministry of Health, I undertake that the above-mentioned study will be conducted in accordance with the principles of this guideline.

Date : 23 / 05 / 2021

190 **Statistical Analyses Plan**

191  
192  
193  
194  
195  
196  
197  
198  
199  
200  
201  
202  
203  
204  
205  
206  
207  
208

All statistical analyses will be performed using Stata, with statistical significance defined as a p-value <0.05.

- 1) The flow of participants through the study will be represented in a CONSORT diagram.
- 2) Baseline characteristics and descriptive data of the outcome measures, stratified by the two groups, will be provided using mean and standard deviation, median and interquartile range (IQR) or count and proportion of participants, depending on the data.
- 3) We will test for significant differences between the groups using t-tests, Wilcoxon Rank Sum test or Chi square/Fisher's exact test, depending on the data.
- 4) In primary analyses, we will use mixed linear regression models. Separate models will be employed for each outcome measure. The models will include group, timepoint, and an interaction term between group and time (group\*time) as fixed effects, and participant's ID as random effect. All models will be tested for normal distribution of the residuals and homoscedasticity. A significant p-value for the time\*group interaction will be interpreted as indicative of an intervention effect. The results will also be presented as marginal mean difference with 95%CI between the two groups at the post-tests, and we will illustrate the changes in the outcome measures between the two groups using the marginal means and 95%CI.
- 5) Additional sensitivity analyses may be performed, and subgroup analyses will be performed to explore a possible impact of adherence to the program.

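### The participant random intercept imposes one variance and one correlation on three unevenly spaced visits, which can misstate the standard errors of the group-by-time contrasts; the stated checks offer no remedy

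*Protocol*

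**What the plan says.** The protocol carries a section headed Statistical Analyses Plan. Its item 4 states: "In primary analyses, we will use mixed linear regression models. Separate models will be employed for each outcome measure". The fixed effects are group, timepoint and their interaction. The participant's "ID as random effect. All models will be tested for normal distribution of the residuals and homoscedasticity". A significant interaction is to be read as an intervention effect, "with statistical significance defined as a p-value <0.05". On presentation: "The results will also be presented as marginal mean difference with 95%CI between the two groups at the post-tests". The plots will "illustrate the changes in the outcome measures between the two groups using the marginal means and 95%CI".

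The visits are set in Materials and Methods: "Two days after the training, the tests will be done again (Posttest 1) in a similar way to the pretest", and then "Eight weeks after Posttest 1, Posttest 2 will be performed using the same parameters". The flowchart puts the pretest in Week 4 and Posttest 1 in Week 4/5, a gap of about one week. Materials and Methods also places the pretest at recruitment, which the flowchart puts in Weeks 1-3, so the first gap could be up to about four weeks.

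Item 4 names no residual covariance, visit-specific variance, robust standard error or action after a failed check.

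**The concern.** A random intercept with independent residuals is compound symmetry. The correlation between pretest and Posttest 1 must equal that between pretest and Posttest 2 and that between the two post-tests, and the variance must be the same at all three visits. Here the gaps are about 1, 8 and 9 weeks by the flowchart. For self-reported distress, burnout and sleep, equal correlation over such different gaps is a strong assumption, and an intervention may also change the spread.

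The assumption reaches the decision rule. With categorical time and pretest as reference, the interaction coefficients are the between-group differences in change from pretest, and their standard errors depend directly on the correlation of each visit pair. Item 4 does not say whether a joint test or a single coefficient decides. A check of residual normality says nothing about correlation between visits. The homoscedasticity check bears on the equal-variance half only, and nothing is said to follow from it.

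**Working it through.** **Inputs from the protocol.** Target 80 per arm with 20% dropout or exclusion; 80/(1 - 0.20) = 100 per arm, which reproduces the stated enrolment. Alpha is 0.05, taken as two-sided because sidedness is not stated. There are three visits. The protocol gives no SD and no correlation, so every value of these below is an assumption.

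**Change-from-pretest contrasts, complete data, equal SDs (SD = 1, n = 80 per arm).**
- True SE = sqrt(4(1 - r)/n), where r is the correlation between pretest and that post-test.
- The random-intercept model uses the mean of the three correlations, r̄, in place of r.
- Ratio of model SE to true SE = sqrt((1 - r̄)/(1 - r)).
- Actual size of a nominal 5% test = 2(1 - Φ(1.96 × ratio)).

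Worked case with correlations 0.80 (pre-P1), 0.60 (P1-P2) and 0.55 (pre-P2): r̄ = 1.95/3 = 0.65, and the model SE is sqrt(4 × 0.35/80) = 0.132 for both contrasts. The true SE is sqrt(4 × 0.20/80) = 0.100 at Posttest 1 and sqrt(4 × 0.45/80) = 0.150 at Posttest 2. The ratios are 1.32 and 0.88.

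| pre-P1 / P1-P2 / pre-P2 | r̄ | Ratio, Posttest 1 | Ratio, Posttest 2 | Size, Posttest 2 contrast | Size, joint 2-df test |
|---|---|---|---|---|---|
| 0.70 / 0.60 / 0.60 | 0.633 | 1.11 | 0.96 | 6.1% | 5.2% |
| 0.80 / 0.60 / 0.55 | 0.650 | 1.32 | 0.88 | 8.4% | 5.7% |
| 0.85 / 0.50 / 0.45 | 0.600 | 1.63 | 0.85 | 9.5% | 6.5% |
| 0.60 / 0.70 / 0.60 | 0.633 | 0.96 | 0.96 | 6.1% | 5.2% |

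The joint-test column is from simulation (400,000 draws). The last row shows a case in which the intervention itself lowers the pre-P1 correlation; both contrasts are then slightly too narrow.

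**Visit-level group differences, complete data.** The true SE at visit k is s_k × sqrt(2/n), where s_k is the SD at that visit. The model uses the average variance over the three visits, so the ratio is sqrt(mean of s²)/s_k. The correlation does not enter.
- SD 1/1/1: sqrt(2/80) = 0.158 for both; ratio 1.00 at both post-tests, coverage 95.0%.
- SD 1/1/1.2: mean variance 3.44/3 = 1.147, root 1.071; ratios 1.07 at Posttest 1 and 0.89 at Posttest 2.
- SD 1/0.9/0.7: mean variance 2.30/3 = 0.767, root 0.876; ratios 0.97 and 1.25.
- SD 1/0.8/0.8: mean variance 2.28/3 = 0.76, root 0.872; ratio 1.09 at both.

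**With dropout.** Assume 100 per arm with completely random loss (80 complete, 10 lost after Posttest 1, 10 lost after pretest), equal SDs and correlations 0.80/0.60/0.55. A sandwich calculation gives visit-level ratios of 1.01 and 0.98 (coverage 95.2% and 94.6%) and change-contrast ratios of 1.30 and 0.88. Over the three decaying sets in the table, the visit-level ratio stays between 0.975 and 1.016.

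**The case against.** A reader might infer that the plotted and tabulated 95% intervals will be too narrow at Posttest 2 and too wide at Posttest 1. The documents do not support that. The intervals that item 4 presents are for marginal means and for group differences at each post-test. With equal variances their standard errors are right on complete data and within about 3% under random dropout. With unequal variances the error can run in either direction, including the reverse of that inference (SD 1/0.9/0.7).

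Three further objections have weight. First, the direction for the change contrasts comes from assumed correlations; the protocol supplies none, and the 0.60/0.70/0.60 case does not show the pattern. If the pretest is really taken at recruitment, the first gap is longer and the decay may be milder, although the spacing remains uneven. Second, if the interaction is tested jointly, the loss of error control is small; sizes of 6-9.5% apply to the Posttest 2 contrast taken alone. Third, independent residuals are the usual reading of item 4, not its words. Residual structure is often left to a fuller analysis plan, and item 5 leaves room for sensitivity analyses.

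These points limit the size of the concern but do not remove it. Item 4 does specify the primary random-effects structure and the checks, and as written that structure is less suitable than an equally simple alternative.

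**Conclusion.** The point holds as a conditional risk with an inexpensive remedy. As written, the primary model forces equal variance and equal correlation on unevenly spaced visits, and its checks neither test the correlation nor lead to any action.

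- For the change-from-pretest contrasts under decaying correlation, standard errors are about 4-15% too small at Posttest 2 and 11-63% too large at Posttest 1.
- The joint interaction test is mildly inflated, to about 5-6.5%.
- The presented visit-level differences are essentially sound if variances are equal. If the SD differs by visit, the SE ratio at Posttest 2 ranged from about 0.89 to 1.25 in the cases tried.

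These figures rest on assumed correlations and SDs, on reading the ID effect as a random intercept with independent residuals, and on categorical time. No direction of error can be asserted for this trial from the protocol alone. For a pilot this is a worthwhile improvement; it does not invalidate the analysis.

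**What to change.** Keep group, categorical timepoint and their interaction as fixed effects. Replace the participant random intercept with an unstructured 3x3 residual covariance within participant, fitted by REML. Alternatively, keep the random intercept and prespecify standard errors clustered on participant, so that inference does not depend on the outcome of the residual checks. Of the two, the unstructured model also weights incomplete records by the estimated covariance, which matters with 20% expected dropout. State whether the interaction is judged by the joint 2-df test or by a named contrast.

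The cost is four extra covariance parameters per model (six instead of two). This is small with 160-200 participants and needs only a change of model specification in Stata. No additional data are required.

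### Every outcome model is primary at p<0.05 with none ranked or adjusted, so a study-level claim that SKY works carries roughly a 12–30% false-positive risk

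*Protocol*

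**What the plan says.** The Statistical Analyses Plan, printed after the Commitment Statement, opens by applying one threshold to all analyses, "with statistical significance defined as a p-value <0.05". Item 4 then sets the main analysis: "In primary analyses, we will use mixed linear regression models". It continues: "Separate models will be employed for each outcome measure". For each model, a significant group-by-time "interaction will be interpreted as indicative of an intervention effect". Item 4 also promises mean differences between groups, with 95% confidence intervals, at the post-tests.

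The outcome measures are listed under Procedures and Variables. There are four questionnaires: DASS-42, PFI, LOT-R and RIS. DASS-42 is described as "A set of three self-report scales designed to measure the negative emotional states of depression, anxiety and stress", and PFI as "A brief instrument to assess both burnout and professional satisfaction in physicians". No questionnaire or subscale is ranked above another, and the number of scores to be modelled is not stated.

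The Rationale section gives a hypothesis covering distress, resilience and other favourable changes, again unranked. It says that the pilot will test this hypothesis as well as feasibility, and that positive results would lead to larger trials.

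**The concern.** The plan fixes three things together: all models are primary, each is judged alone at 0.05, and each significant interaction is read as an effect of the intervention. It does not say which score decides whether the trial has succeeded. With several primary tests of equal rank, a team can report that the intervention works when any one of them crosses the line, and nothing in the text prevents this.

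The overall conclusion, and possibly the decision to go on to larger trials, is at stake. If SKY had no effect on any score, the chance of being able to make some such claim would be well above the 5% that the threshold suggests. Choosing the decisive score after results are known would not repair this credibly.

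**Working it through.** **The plan's own figures.** The protocol gives no power, effect size, standard deviation or familywise error rate. The one design figure that can be rebuilt is enrolment: 80 / (1 − 0.20) = 100 per group, as stated. It has no bearing on multiplicity. The figure to compare against is the 0.05 threshold.

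**Inputs.**
- Level per test: 0.05 (opening line of the Statistical Analyses Plan). Sidedness is not stated; two-sided is assumed.
- Number of scores, k, inferred from Procedures and Variables:
  - k = 4 with one score per questionnaire;
  - k = 6 with three DASS-42 scales, one PFI score, LOT-R and RIS;
  - k = 7 if PFI is split into burnout and professional satisfaction.
- One interaction test per score. There are three assessment times, so the interaction has 2 degrees of freedom if time is categorical.
- Correlation between the test statistics of different scores: not given. An equal correlation from 0 to 0.8 is assumed.

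**Independent scores.** The chance of at least one false positive is 1 − 0.95^k:
- k = 4: 1 − 0.8145 = 18.5%
- k = 6: 1 − 0.7351 = 26.5%
- k = 7: 1 − 0.6983 = 30.2%

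**Correlated scores.** These come from 400,000 simulated null trials for each case, with a joint 2-df test per score and equal correlation between scores:

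| Assumed correlation | k = 4 | k = 6 | k = 7 |
|---|---|---|---|
| 0.3 | 17.4% | 24.3% | 27.4% |
| 0.5 | 15.8% | 21.2% | 23.5% |
| 0.7 | 13.3% | 17.0% | 18.3% |
| 0.8 | 11.7% | 14.3% | 15.4% |

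Tests with 1 df give results within about 1 percentage point. A less uniform pattern, with correlation 0.7 within a questionnaire and 0.4 between questionnaires, gives 21.4% for 6 scores and 23.8% for 7.

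**Under the remedies.** One primary score with one test gives 5%. Bonferroni at 0.05/k (0.0125, 0.0083 and 0.0071 for k = 4, 6 and 7) gives 4.9% under independence and at most 5% under any correlation. Holm also holds 5%, and its first step uses the same threshold as Bonferroni.

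**Power cost of adjusting all 7.** A single score with 80% power at two-sided 0.05 has an expected z of 1.960 + 0.842 = 2.802. The critical value at 0.05/7 = 0.0071 is 2.690. Power at Holm's first step is Φ(2.802 − 2.690) = Φ(0.112), about 54% (normal approximation, 1 df). This is the worst case, because later Holm steps are less strict.

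**The case against.** The best defence is that item 4 reads each p-value within its own model. Taken that way, each statement concerns one score and has 5% error. That is correct, and it limits the point: the inflation applies only to a study-level claim. A reader might infer that the plan declares the trial a success if any one of 7 tests is significant, but no sentence says so. The remark about larger trials is tied to no test, and the same sentence of the Rationale also mentions feasibility. What stands is that nothing ties the overall conclusion to one score either.

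Second, this is a pilot, and item 4 promises confidence intervals as well as p-values. Whether a pilot needs familywise control is partly a matter of judgement. This lowers the severity. It does not remove the point, because the protocol says the pilot will test its hypothesis and item 4 calls these analyses primary.

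Third, a reader might take 18–30% as the plain error rate. Read as 4 to 7 scores, that range assumes independence, which is unlikely for related self-report scores from the same people, and it leaves out the correlated 4-score cases. The count of 7 is itself a reading of the questionnaire descriptions.

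Three further extensions are tempting and are not supported:
- Item 3 says "We will test for significant differences between the groups using t-tests, Wilcoxon Rank Sum test". This could be taken as a second set of outcome tests, but the item names no outcome or time and directly follows the baseline and descriptive item, so it may cover baseline only.
- Materials and Methods says "The data obtained will be compared within and between the experimental and control groups at these three different times". This announces comparisons within groups but no within-group p-value or claim, so it cannot be counted as further tests.
- Reading the two post-test interaction terms separately would give 32–49% under independence (correlation 0.5 assumed between the two terms). Item 4, however, speaks of a single p-value for the interaction.

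**Conclusion.** The point holds for a study-level claim. With 4 to 7 primary scores of equal rank, each tested at 0.05, the chance of at least one false positive is 18.5–30.2% if the scores are independent and about 12–27% at assumed correlations of 0.3 to 0.8. The lowest case computed is 11.7%, more than twice the nominal 5%.

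The result rests on three assumptions that the protocol does not settle: the number of scores, their correlation, and one joint interaction test per score. The error of each per-score test remains 5%. None of these figures includes anything from item 3 or from within-group comparisons.

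This should be fixed, because the rule is written into the plan and is cheap to change. It is not a defect that invalidates a pilot reporting estimates with confidence intervals.

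**What to change.** In item 4, before data are seen:
1. Name one primary score and one primary contrast or time point, tested at 0.05. The choice is the team's; a DASS-42 scale at Posttest 2 is one option.
2. List the scores that will be analysed, and call the remaining ones secondary. Either apply Holm adjustment to them or report estimates with 95% confidence intervals only.
3. In the Rationale section, tie positive results to the primary analysis.

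The change needs no new data, visits or participants. The cost is that the other scores can no longer support a claim at an unadjusted p<0.05. If the team prefers not to choose, Holm across all 7 scores also controls the error, but a score planned with 80% power could fall to about 54% at the first step. Naming one primary is therefore the better option.

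### Item 4 tests the group-by-time interaction but presents post-test differences that are not adjusted for the pretest, so p-value and interval can disagree and the interval is wider than it need be

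*Protocol*

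**What the plan says.** The Statistical Analyses Plan at the end of the protocol specifies the primary analysis in item 4. A separate mixed linear model is fitted for each outcome: "The models will include group, timepoint, and an interaction term between group and time", with participant as random effect. A significant interaction is read as an intervention effect, "with statistical significance defined as a p-value <0.05". The effect size is presented differently: "The results will also be presented as marginal mean difference with 95%CI between the two groups at the post-tests".

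Under Materials and Methods, "Both groups will be pretested at the time of recruitment into the study". Posttest 1 follows two days after training and Posttest 2 eight weeks after that. Results are to be "compared within and between the experimental and control groups at these three different times". The pretest is therefore one of three modelled timepoints. It is neither a covariate nor constrained to be equal between arms. Item 4 does not name a difference in change as the reported effect, and it gives no rule for the case where the interaction and the post-test intervals point different ways.

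**The concern.** In this model the group difference at a post-test is the group coefficient (the difference at pretest) plus the interaction coefficient for that visit. The interaction test uses only the interaction coefficients. The reported interval therefore contains chance pretest imbalance that the test has subtracted out. With 100 per arm, that imbalance has a 95% range of ±1.96 × √(2/100) = ±0.28 SD.

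If time is categorical, the interaction is a joint 2-df test. It does not say which arm did better or when. A response present two days after training and gone eight weeks later can make it significant just as readily as one that lasts.

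Readers could then meet a significant p-value beside two intervals that include zero, or the reverse, with no stated way to resolve it. The protocol's rationale says positive results will be the basis for larger trials, so the estimate and its interval are what the next study would use.

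**Working it through.** **Inputs from the protocol.** Significance level 0.05 (two-sided assumed); 1:1 allocation; three timepoints; "The target for each group is 80 subjects, but to account for dropout/exclusion, 100 subjects per group will be included", with 20% expected loss.

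**The plan's own figure.** 80 / (1 − 0.20) = 100 per arm, which reproduces. The protocol gives no SD, effect size or pre-post correlation, so those below are assumptions.

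**Assumptions.** Outcome in SD units; equal correlation r between visits, as a random intercept implies; n = 80 per arm with complete data; true effect 0.4 SD.

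**Standard errors of the group contrast at one post-test.**
- Unadjusted post-test difference: √(2/n) = √(2/80) = 0.158, whatever r is.
- Difference in change: √(2/n) × √(2(1 − r)).
- Baseline-adjusted: √(2/n) × √(1 − r²).

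The adjusted interval is narrower than the unadjusted one by 1 − √(1 − r²). The adjusted SE is smaller than the change SE by 1 − √((1 + r)/2).

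| r | SE unadjusted | SE change | SE adjusted | Narrower than unadjusted | SE smaller than change |
|---|---|---|---|---|---|
| 0.3 | 0.158 | 0.187 | 0.151 | 4.6% | 19% |
| 0.5 | 0.158 | 0.158 | 0.137 | 13.4% | 13% |
| 0.6 | 0.158 | 0.141 | 0.126 | 20.0% | 11% |
| 0.7 | 0.158 | 0.122 | 0.113 | 28.6% | 8% |

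At r = 0.6 the 95% half-width falls from 1.96 × 0.1581 = 0.31 SD to 1.96 × 0.1265 = 0.25 SD.

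**Power of the planned decision rule.** For group differences of 0, 0.4 and 0.4 SD at the three visits, the 2-df non-centrality is (n/2) × Σ(difference − mean difference)² / (1 − r) = 40 × (2/3) × 0.16 / (1 − r) = 4.27/(1 − r). The comparator is one adjusted contrast, with power Φ(0.4/SE − 1.96).

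| r | Planned interaction, 2 df | One adjusted post-test contrast |
|---|---|---|
| 0.3 | 59.1% | 75.6% |
| 0.5 | 74.7% | 83.2% |
| 0.6 | 84.1% | 88.5% |
| 0.7 | 93.2% | 94.3% |

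At r = 0.8 the two are level (99.0% and 98.8%).

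**Timing.** For differences of 0, 0.4 and 0 SD, the sum of squares about the mean is again (2/3) × 0.16. The interaction therefore has the same power, 75% at r = 0.5 and 84% at r = 0.6, when nothing remains at Posttest 2.

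**Disagreement between test and intervals.** This was simulated with 6,000 trials per setting, n = 80 per arm, pairing the 2-df interaction with the two unadjusted post-test intervals.

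| Effect at Posttest 1, 2 | r | Interaction significant, neither interval excludes 0 | An interval excludes 0, interaction not significant |
|---|---|---|---|
| 0.4, 0.4 SD | 0.3 / 0.5 / 0.7 | 3.3 / 7.4 / 15.4% | 32.6 / 19.1 / 4.8% |
| 0.2, 0.4 SD | 0.3 / 0.5 / 0.7 | 4.3 / 9.9 / 20.4% | 32.8 / 22.4 / 8.2% |

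Adding the two columns, the pair disagrees in about 20 to 37% of trials with a real effect. With no effect, at least one of the two intervals excludes zero in about 9 to 10% of trials, against about 5% for the interaction. Part of the right-hand column therefore arises because two intervals are set against one test.

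**The case against.** The strongest reply is that group, time and group-by-time is a standard and valid analysis, that this is a pilot, and that the interaction already handles the pretest. Much of that stands. A reader might infer that the pretest goes unused. It does not: it is a modelled timepoint, and the interaction subtracts it. What lacks adjustment is the reported post-test difference. Even that is not strictly the raw difference once people drop out, because likelihood estimation borrows from earlier visits. At r = 0.6, with 100 enrolled and 80 completing, the variance of the Posttest 2 mean is about 0.91 to 0.93 of the completers-only value.

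A reader might also set the 71.6% power of the unadjusted post-test difference against 88.5% for the adjusted one at r = 0.6 and conclude that the trial loses 17 points. The documents do not support that, because the unadjusted difference is not the decision rule. The interaction is, and with a sustained effect it already has 84%. Its less favourable case is an effect at Posttest 1 half that at Posttest 2, where the 2-df test has less power than a single change contrast.

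Reporting differences in change from the planned model would also align estimate and test more closely. That is a fair minimal cure, but it leaves an SE that adjustment would cut by 8 to 19%.

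Convention and pilot status do not remove the mismatch between what is tested and what is reported.

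**Conclusion.** The point holds as one of efficiency and interpretation, and the change should be made. Item 4 tests one quantity and presents another, and the presented interval is wider than the same data allow for any positive correlation.

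The size depends on a correlation that the protocol does not give: about 5% of interval width at 0.3 and 29% at 0.7. The power gain over the planned test runs from about 17 points at 0.3 to 1 point at 0.7, for an assumed sustained 0.4 SD effect. The 2-df reading is inferred from categorical timepoints. A linear time term would give a 1-df slope test, which would still not match the post-test differences.

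A reader might take the retained pretest imbalance as bias. It is not: under randomisation the unadjusted post-test difference is unbiased. Nor does the point require Posttest 2 to become the single test, since the choice of primary timepoint is a separate scientific decision. The sample-size arithmetic is unaffected.

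**What to change.** In item 4, keep the mixed model but enter the pretest score as a covariate, with Posttest 1 and Posttest 2 as the outcomes and group, timepoint and group-by-timepoint as fixed effects. Take both the p-value and the 95% CI for each post-test from the adjusted group contrast at that visit.

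An alternative keeps all three visits and constrains pretest means to be equal across arms, by dropping the group main effect and keeping the group-by-post-test terms. This is sound only if the pretest precedes knowledge of allocation. Materials and Methods places the pretest at recruitment, the timeline places it in Week 4 after inclusion in Weeks 1 to 3, and neither says when randomisation takes place. The order should be stated before the constraint is used.

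The investigators should name in advance which post-test is primary, because reading two contrasts each at 0.05 does not hold the overall error rate that a single interaction test holds. The interaction can stay as a supporting result.

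The cost is one changed model line in Stata and a sentence in item 4. No new data are needed.
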